# The efficacy, safety and cost-effectiveness of hydroxychloroquine, sulfasalazine, methotrexate triple therapy in preventing relapse among patients with rheumatoid arthritis achieving clinical remission or low disease activity: the study protocol of a randomized controlled clinical Trial (ESCoRT study)

**DOI:** 10.1186/s12911-021-01449-2

**Published:** 2021-03-04

**Keywords:** Rheumatoid arthritis, Pharmaceutical economics analysis, Cost-effectiveness analysis, Cost-utility analysis, Relapse

## Abstract

**Background:**

Tumor necrosis factor α inhibitors (TNFi) is effective for rheumatoid arthritis (RA) patients who fail to conventional synthetic disease-modifying anti-rheumatic drugs (csDMARDs). Because of high cost, the discontinuation is common but often lead to disease relapse. The study aims to investigate, if the combination therapy of csDMARDs is more effective in reducing disease relapse than methotrexate (MTX) monotherapy, and more cost-effective than continuing TNFi and MTX.

**Methods:**

It will be a two-stage trial. In the first stage, all RA patients who failed to csDMARDs treatment [disease activity score 28 (DAS28)-CRP > 3.2] will receive MTX plus TNFi for no more than 12 weeks. Patients achieving DAS28-CRP < 3.2 during the first stage will be randomized into three groups at 1:1:1 ratio: (A) add hydroxychloroquine (HCQ) and sulfasalazine (SSZ) for the first 12 weeks and then remove TNFi but continue other treatments for the next 48 weeks; (B) maintain TNFi + MTX for 60 weeks; and (C) maintain TNFi + MTX for the first 12 weeks and then remove TNFi but continue MTX monotherapy for the next 48 weeks. The primary outcome will be disease relapse (DAS28-CRP increases by at least 0.6 and > 3.2). Secondary outcomes will include the incremental cost per reducing 1 case of relapse; patient reported intolerance to the treatment; adverse events; change of mean disease activity measured by DAS28, clinical disease activity index (CDAI) and simplified disease activity index (SDAI); the proportion of modified Sharp score increase < 0.3; ultrasound-detected remission in hands; Health Assessment Questionnaire Disability Index (HAQ-DI) and health related quality of life [the five-level EuroQol-5D (EQ-5D-5L) and short form-6D (SF-6D)].

**Discussion:**

The aim of this trail will be to seek effective treatment options of preventing relapse of RA. The results of the current study may provide an instructive recommendation for more economical application of TNFi treatment in RA.

*Trial registration* NCT, NCT02320630. Registered on 16 December 2014. https://register.clinicaltrials.gov/prs/app/action/LoginUser?ts=3&cx=-jg9qo2.

## Background

Rheumatoid arthritis (RA) will cause joints deformity and functional loss if not treated with early effective therapy. Only 30% to 40% of RA patients could achieve good response with the treatment of methotrexate (MTX) monotherapy [1]. The treatment effectiveness has been greatly improved by biological disease-modifying anti-rheumatic drugs (bDMARDs), especially Tumor Necrosis Factor α inhibitors (TNFi). “Treat to target” (T-to-T), achieving clinical remission (CR) or low disease activity (LDA) alternatively for long term, has become the core strategy of RA treatment. According to the most recent recommendations by both European League against Rheumatism (EULAR) and American College of Rheumatology (ACR), after the failure of conventional synthetic disease-modifying anti-rheumatic drugs (csDMARDs), the application of biological agents, especially TNFi, is recommended [2].

The discontinuation of TNFi often leads to increased relapse rate of RA. In a recently published clinical trial, early RA patients who had achieved clinical remission or low disease activity by adalimumab and MTX were randomized to maintain or discontinue adalimumab. During a 78-week observation, 81% of those who stopped adalimumab maintained LDA, comparing to 91% of those who continue to receive adalimumab [3]. It was also reported that for established RA patients who have achieved CR or LDA by TNFi combined with MTX, 24% to 85% suffered from disease relapse after discontinuation of TNFi [4–7].

However, due to the high cost, the demand for discontinuation of TNFi is common. For patients who have achieved the treatment target, strategies to balance the expense and the risk of relapse are urgently needed. It has been reported that, in RA patients who achieved CR with TNFi combining MTX, the proportion for patients who maintained CR with half-dose of TNFi was comparable to those with full dose, and both were higher than those who discontinued TNFi [8].

An increasing number of studies showed that the efficacy of csDMARDs combination therapy is superior to monotherapy [9]. The classical combination strategy of MTX plus hydroxychloroquine (HCQ) and sulafasalazine (SSZ) provided good response and safety [10, 11]. It has been reported that 77% refractory RA patients had 50 percent improvement at nine months without major drug toxicity with MTX + HCQ + SSZ triple therapy [10]. Nevertheless, the BeSt study showed that there was little difference between csDMARD monotherapy and combination therapy [12]. A previous study showed that combination therapy of MTX and cyclosporin could not prevent relapse in 58% RA patients after discontinued biological DMARD [4]. In that study, cyclosporin was just initiated at the discontinuation of TNFi. However, considering the delayed efficacy of csDMARDs, it is preferable to overlap csDMARDs and TNFi for several weeks before discontinuation of TNFi.

Long-term therapy of bDMARDs poses a heavy burden on RA patients and the society. The commonly used csDMARDs are much cheaper than biologics [13]. An investigation showed that only 9% of Chinese RA patients received biological DMARDs. However, the cost of biologics accounted for 49% of the total cost for RA treatment medications. Due to lack of high quality research, it is still under debate whether the benefit is worth such high cost.

This 1:1:1 randomized enrollment parallel group study aims to investigate, among RA patients who are refractory to csDMARDs but have achieved CR or LDA after treatment with TNFi and MTX, if the triple therapy of MTX + HCQ + SSZ is more effective in reducing the relapse rate than MTX monotherapy, and more cost-effective than continuing the treatment of TNFi and MTX.

## Methods/design

### Study design

This will be a two-stage study. The first stage will serve as an induction treatment with TNFi plus MTX for no more than 12 weeks. Patients who have achieved CR or LDA [defined as disease activity score 28 (DAS28)-CRP ≤ 3.2] in 12 weeks will enter the second stage at the time of CR/LDA achieved. The second stage will be a multiple-center, randomized, outcome assessment blinded, parallel controlled clinical trial. All eligible participants will be randomly allocated to three arms at a ratio of 1:1:1 to receive different treatment strategies for 60 weeks or until relapse.

This study will be expected to be conducted from October 2015 to September 2022. The first patient was recruited on Oct 8, 2015 and the last patient is planned to be recruited by Sep 30, 2021. The study flow-chart is shown in Fig. 1.

**Fig. 1 Fig1:**
[figure not shown]
The study flow chart. Note: for patients who relapse during follow up, the study treatments will be stopped and patients will be referred to appropriate alternative treatments and follow up will be continued for cost data collection. RA: Rheumatoid Arthritis; csDMARDs: conventional synthetic disease-modifying anti-rheumatic drugs; MTX: methotrexate; HCQ: hydroxychloroquine; SSZ: sulfasalazine; TNFi: Tumor necrosis factor α inhibitors; CR:clinical remission; LDA: low disease activity

### Eligibility criteria

Inclusion criteriaFulfill the 2010 EULAR/ACR diagnostic criteria of RA;Disease duration > 6 months;≥18 and≤70 years old;Use of single or combination of csDMARDs with standard dosage (must including MTX and/or leflunomide) for more than 3 months;DAS28-CRP> 3.2;Sign informed consent form (ICF).Exclusion criteriaReceive therapies of any of the below:Large surgical operations within 8 weeks (including articular operation) or in plan;Any former use of cell elimination therapy, including CAMPATH, anti-CD4, anti-CD5, anti-CD3, anti-CDl9, anti-CD20 and the research drug in the current study;γ-immunoglobulin, plasmapheresis, retuximab or IL-6 inhibitor within 6 months;Any form of glucocortocoid injection therapy within 4 weeks;Live vaccines or live attenuated vaccines within 4 weeks;Any alkylating agents including cyclophosphamide and nitrogen mustard, or total lymphoid irradiation therapy;Complicate with any other diseases or organ/tissue damages as follows:Autoimmune diseases other than RA. Patients combining with primary SjÖgren syndrome (pSS) are permitted;Severe or uncontrolled cardiac disease, nervous system disease, pulmonary disease (including chronic obstructive pulmonary disease and interstitial lung disease), renal disease, liver disease, endocrine disease (including diabetes mellitus) and gastrointestinal disease;Diseases that need oral or injection therapy of glucocorticoid, including but not limited to bronchial asthma, psoriasis and inflammatory bowel disease;Current or relapsing infections (include but not limited to tuberculosis or atypical mycobacterium disease, granuloma in chest X ray, type B or type C hepatitis, human immuno-deficiency virus (HIV), Zoster, but patients with nail fungal infection are permitted). Infection that needs hospitalization or intravenous antibiotics within 4 weeks, or oral antibiotics within 2 weeks;Malignant disease, including solid tumor and hematological malignancies (but patients with moved or cured skin basal cell carcinoma are permitted);Nerve damage or other painful disease that may affect pain evaluation;Laboratory abnormalities:Serum creatinine> 130umol/L;Alanine aminotransferase (ALT) or aspartate transaminase (AST) > 2 upper limit of normal, or total bilirubin> upper limit of normal;Platelet <100 × 109/L, or white blood cell count (WBC) <3 × 109/L;Interstitial lung disease: confirmed by chest X ray;Double hands X ray shows ACR imaging stage IV;Allergic to or have severe adverse reaction with any experimental drug in the induction or randomization stage;Pregnant or plan to be pregnant in 2 years, or nursing mothers.

Participants will be recruited into this study from seven participating research centers. As soon as the patients achieve DAS28-CRP ≤ 3.2 during the induction phase, they will be further recruited into the second stage of randomized phase. Patients who do not achieve clinical remission or LDA by the end of 12 weeks of the induction phase will exit the study and receive empirical treatment.

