### Randomization

The blocked randomization, stratified by study center and gender of patients, will be performed centrally when CR or LDA is achieved (V0, week 0). The staffs responsible for randomization will obtain the group allocation code from the Peking University Clinical Research Institute (PUCRI) through an Interactive Web Response System (IWRS).

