#### Sample size estimation

According to the study purposes, a superiority design was considered appropriate. Our hypothesis is that the relapse rate in group A (triple therapy group) will be lower than that in group C (MTX monotherapy group) in 60 weeks after randomization.

Sample size was calculated by PASS 11.0. It was reported that for patients with established RA achieving CR or LDA by TNFi combined with MTX, 24% to 85% suffered from disease relapse after discontinuation of TNFi [4–7]. When combined csDMARDs preserved after TNFi removed, the rate of relapse was 51.2–58% [4, 7]. We assume that adding HCQ + SSZ 3 months before the removal of TNFi may somehow decrease the relapse. Accordingly, we expect the relapse rate as 50% in patients in triple therapy group, and 74% in MTX monotherapy group. With a power of 0.8 and a significance level of 0.05 (two-sides), using a 1:1:1 treatment allocation of enrollment, to detect the difference of relapse rate between the two groups, the required sample size is 61 for each group. Given the estimated dropout rate of 20%, we intend to recruit a total of 240 subjects (80 for each group).

We assume that the relapse rate may be similar between group A and group B (TNFi maintenance therapy group), and the cost-effectiveness may be better in group A than in group B. The relapse rate and cost-effective comparison between group A and group B will be exploratory and there was no relevant research hypothesis, so the sample size was not calculated by it.

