#### Statistical analysis

All statistical analyses will be performed using SAS 9.2.

The compatibility of baseline data among three groups will be checked. Student’s t-test or Wilcoxon rank sum test will be used for quantitative variables. Chi-square test or Fisher’s exact test will be used for categorical variables. The Cochran–Mantel– Haenszel test or the Wilcoxon rank sum test will be used for ordinal variables.

To compare the relapse rate between triple therapy group and MTX monotherapy group, the intention-to-treat principle will be followed. Considering the influence of central effect, the collected data will be estimated by mantel Haenszel method with stratification by study centers. Kaplan–Meier curves will be used to show the differences of relapse rate among three groups. The disease activity changes and other continuous secondary outcomes (Sharp score, ultrasonic Doppler score and HAQ-DI score) will be compared between the study groups using the covariance analysis model. Per protocol analyses will also be conducted as sensitivity analyses.

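### Primary A vs C comparison leaves out disease duration, although any rheumatoid arthritis (RA) of more than 6 months is eligible and the Background suggests lower relapse in early disease

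*Protocol article*

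**What the plan says.** - **Eligibility criteria:** disease duration has a floor only, "Disease duration > 6 months", with no upper limit. Prior treatment need be no longer than this: "Use of single or combination of csDMARDs with standard dosage (must including MTX and/or leflunomide) for more than 3 months". Early and established RA are not defined.
- **Background:** for early RA, "81% of those who stopped adalimumab maintained LDA, comparing to 91% of those who continue to receive adalimumab", over 78 weeks. For long-standing disease, "for established RA patients who have achieved CR or LDA by TNFi combined with MTX, 24% to 85% suffered from disease relapse" once the TNFi was withdrawn.
- **Sample size estimation:** only the second source is used ("for patients with established RA achieving CR or LDA by TNFi combined with MTX, 24% to 85% suffered from disease relapse"). The assumed rates are 50% in group A and 74% in group C, giving 61 per group, and 80 after a 20% dropout allowance.
- **Randomization:** "The blocked randomization, stratified by study center and gender of patients".
- **Statistical analysis:** for A vs C under intention to treat, "the collected data will be estimated by mantel Haenszel method with stratification by study centers".

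Disease duration enters neither the randomisation strata nor the primary analysis.

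**The concern.** The protocol does not leave the primary method open; it names one, with centre as the only stratifier. Its own Background gives some reason to think that disease duration predicts relapse after TNFi withdrawal. Where a baseline variable predicts the outcome, an analysis that omits it carries avoidable variance, and a chance imbalance between A and C goes uncorrected in the estimate. At stake is the precision of the primary relapse difference, not its validity. There is also a mismatch of description: the rates used for sizing are drawn from established RA, while the entry criteria are wider.

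**Working it through.** **Inputs from the protocol.** Relapse 50% (A) and 74% (C), two-sided 0.05, power 0.80, 61 per group, 80 with dropout (Sample size estimation). Early RA after stopping: 100% − 81% = 19% lost low disease activity; on continued TNFi 100% − 91% = 9% (Background).

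**Assumptions, not in the protocol.** The early share e. The early-RA rate in C, taken as 19%. The early-RA rate in A, taken as 12.8% (same ratio as 50/74: 0.19 × 50/74) or 9% (as on continued TNFi). All other patients at 74% and 50%.

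**Step 1: the plan's own figure.** Unpooled two-proportion formula:

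n = (1.960 + 0.842)² × (0.50×0.50 + 0.74×0.26) / 0.24² = 7.849 × 0.4424 / 0.0576 = 60.28, rounded up to 61. Then 61/0.8 = 76.25, so 77; the planned 80 covers it. The pooled formula gives 64, and 64/0.8 = 80. The sizing is sound on its inputs.

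**Step 2: precision gained by adjustment.** With each arm a mixture, p = e·p_early + (1−e)·p_other:

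- V_unadj = sum over arms of p(1−p)
- V_adj = sum over arms of the share-weighted p(1−p) within each class
- narrowing = 1 − √(V_adj/V_unadj)

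At e = 10%, early A 12.8%: C = 0.9×0.74 + 0.1×0.19 = 0.685; A = 0.9×0.50 + 0.1×0.128 = 0.463. V_unadj = 0.2486 + 0.2158 = 0.4644. V_adj = 0.9×0.4424 + 0.1×(0.1119 + 0.1539) = 0.4247. Narrowing = 1 − √0.9146 = 4.4%.

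| Early share | Early rate in A | Pooled C | V_unadj | V_adj | Narrower by |
|---|---|---|---|---|---|
| 10% | 12.8% | 68.5% | 0.4644 | 0.4247 | 4.4% |
| 10% | 9% | 68.5% | 0.4641 | 0.4217 | 4.7% |
| 20% | 12.8% | 63.0% | 0.4776 | 0.4071 | 7.7% |
| 20% | 9% | 63.0% | 0.4764 | 0.4011 | 8.2% |

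In points, with 61 per arm and 12.8% in early A, the 95% half-width 1.96·√(V/61) goes from 17.1 to 16.4 at a 10% share, and from 17.3 to 16.0 at 20%.

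**Step 3: how far this depends on the contrast.** Keeping the 50/74 ratio in A and shares of 10-30%, the narrowing is 2-5% if the early rate in C is 35%, and 1-2% if it is 50%. These figures assume a perfectly classified two-class factor. In a simulation with continuous log duration the estimate was unbiased; its standard error was about 5% smaller if the Background contrast holds and about unchanged if duration is weakly prognostic.

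**Step 4: power, under the same kind of assumption.** Here the early rate in A ranges from no effect (19%) through the same risk ratio (12.8%) to the same odds ratio (7.6%), with the pooled-variance formula and no adjustment.

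| Early share | 61 per arm | 80 per arm |
|---|---|---|
| 0% | 0.79 | 0.89 |
| 10% | 0.68-0.72 | 0.80-0.83 |
| 20% | 0.57-0.66 | 0.69-0.78 |

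With all 80 per arm analysed, power falls to 0.80 at an early share of about 10% (no effect), 12% (same risk ratio) or 17% (same odds ratio).

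**The case against.** The strongest reply has three parts.

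*The contrast is weak evidence.* It compares different studies. The 19% is a complement, not a printed relapse rate; it concerns loss of low disease activity over 78 weeks, whereas relapse here is a DAS28-CRP rise of at least 0.6 to above 3.2, over 60 weeks. The Background does not describe those patients as csDMARD failures, which this trial requires. The established-RA range starts at 24%, only 5 points above 19%, and itself spans 61 points. All of this stands. It means that duration may be prognostic, not that it is known to be, and it is why the gain must be given as a range reaching down to nil.

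*The planned test is already valid, and covariates can wait for the analysis plan.* Randomisation protects the Mantel-Haenszel comparison, and its standard error already allows for chance imbalance. That stands, so this is an improvement and not the repair of an error. But the article does fix the primary method and its single stratifier, so commenting on that choice is fair.

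*Exact duration may not be on file.* Eligibility needs only the knowledge that it exceeds 6 months. That is correct; the history taken at S1 is the natural source, and its completeness should be checked.

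A reader might go further and infer that the trial misses its stated 80% power, or reaches it only if no early RA is enrolled. The document does not support this. It gives neither the early share nor a triple-therapy rate in early RA, it states 74% and 50% for the arms as a whole, and analysis of all 80 per arm would keep 80% power up to a share of roughly 10-17%.

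**Conclusion.** The point holds as a low-cost improvement. Entry is wide on disease duration, the Background suggests that duration may matter for relapse, and the primary analysis does not use it. The benefit is modest: an interval about 4-5% narrower at a 10% early share and about 8% at 20%, resting on 19% vs 74% in group C and perfect classification. It is less with a continuous covariate, and near nil if duration is weakly prognostic.

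A failure of power is not established, and 61 and 80 per group stand on their inputs. What can be said is conditional: if a sizeable share of enrolled patients has early RA and relapses at rates like those in the Background, power would be lower than stated. The 80-per-arm figures also need an outcome for every randomised patient; at 61 evaluable per arm there is no such reserve.

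**What to change.** **Statistical analysis.** Before database lock, specify that the primary A vs C comparison adjusts for baseline disease duration (for example log years) together with centre. One suitable form is a logistic model reported as the standardised 60-week relapse difference with its 95% confidence interval. Keep the centre-stratified Mantel-Haenszel result as a supporting analysis. Confirm first, without reference to outcome by arm, that duration is recorded for all randomised patients.

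**Sample size estimation (optional note).** State that 74% and 50% come from established-RA sources and that power would be lower if a sizeable share of patients has early RA. The disease-duration mix of the 123 patients already randomised, pooled over arms, would show whether this matters.

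**Cost.** A few sentences and one baseline covariate; no extra patients or visits. The downside is a model-based primary estimate in place of a plain stratified table, which the supporting analysis offsets.

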### Randomization

The blocked randomization, stratified by study center and gender of patients, will be performed centrally when CR or LDA is achieved (V0, week 0). The staffs responsible for randomization will obtain the group allocation code from the Peking University Clinical Research Institute (PUCRI) through an Interactive Web Response System (IWRS).

### Interventions

Enrolled subjects will receive oral MTX 10–20 mg once a week and subcutaneous injection of TNFi 50 mg once a week in the induction stage.

Patients who did not receive MTX before recruitment, will initiate MTX 10 mg per week at enrollment. In the induction stage, MTX will be allowed to be titrated up to 20 mg per week if the patient do not achieve DAS28-CRP ≤ 3.2.

The three treatment strategies at the randomized stage will be:

Group A: add HCQ 200 mg twice per day and SSZ 1000 mg twice per day for the first 12 weeks and then remove TNFi but continue MTX + HCQ + SSZ for the next 48 weeks (intervention group, triple therapy group);

Group B: maintain TNFi + MTX for all the next 60 weeks (control group 1, TNFi maintenance group);

Group C: maintain TNFi + MTX for the first 12 weeks and then remove TNFi but continue MTX monotherapy for the next 48 weeks (control group 2, MTX monotherapy group).

### Concomitant medications

#### Concomitant medication not permitted

Glucocorticoids and other DMARDs, including leflunomide, azathioprine, tripterygium, cyclosporine, and other biological agents.

#### Concomitant medication permitted

NSAIDs will be permitted, but the drug name, dosage and time of treatment should be recorded.

Anti-hypertension medications, anti-diabetic agents, aspirin and β-blocker will be permitted.

All the concomitant medications used during the study should be recorded in the case report form (CRF).

